## Abstract

Mitochondrial dysfunction, a hallmark of metabolic disturbances in the skeletal muscle, has previously been studied in health participants using invasive muscle biopsy and/or time consuming, high-cost magnetic resonance spectroscopy. However, less is understood regarding mitochondrial dysfunction in patients with cancer. Near infrared spectroscopy (NIRS) is a non-invasive and cost-effective approach to assessing mitochondrial function of skeletal muscle by measuring oxygenated and deoxygenated hemoglobin and calculating the resulting tissue saturation index. NIRS has not yet been utilized to evaluate skeletal muscle change in cancer patients throughout chemotherapy. Therefore, we plan to conduct a single center clinical trial, using an observational mixed model repeated measures design to evaluate the change in mitochondrial oxidative capacity from baseline and throughout progression of an oncologist-prescribed chemotherapy regimen. Evaluation of mitochondrial function will be performed by taking real-time, NIRS in-situ measurements within the working muscle during stationary cycling exercise and subsequent recovery periods (e.g., “on” kinetics and “off” kinetics). We also plan to observe if there is a difference in mitochondrial oxidative capacity between different chemotherapy regimens across different patients. This pilot study will provide information on the feasibility of capturing on/off kinetics mitochondrial function data longitudinally using NIRS in patients newly diagnosed with breast or gynecological cancer, provide preliminary data for future extramural funding, as well as inform the scientific community of results through dissemination via conferences and peer-reviewed journal publications.

This clinical trial has been registered with clinicaltrials.gov (Identifier: NCT006672497). Data collection started on July 26, 2021 and is ongoing through March 27, 2026. The authors confirm that all ongoing and related trials for this observation trial (no drug or intervention) are registered.

## Introduction

In the United States, more than 3.8 million women are currently receiving chemotherapy treatment, or have completed treatment, for breast or gynecological cancer [1]. Fortunately, over the past 25 years, the ability to detect and treat cancer has allowed breast cancer 5-year survivor rates to increase to 85 [1], ovarian cancer 5-year survivor rates to increase to 49% [2], and uterine cancer 5-year survivor rates to increase to 81% [3]. Unfortunately, while chemotherapy has improved survival rates amongst patients with breast and gynecological cancer, side effects include unfavorable body composition changes [4], increases in fatigue [5], reductions in physical functioning [6], and decreased quality of life (QOL) [7]. Many of these symptoms may be due to post-chemotherapy cachexia [8–10]. According to the National Cancer Institute, cachexia is estimated to occur in up to 80% of people with advanced cancer [8,11] and involves reduced size and content of mitochondria [12,13] and subsequent deterioration of mitochondrial function and its oxidative capacity associated with reduced energy production for physical functioning [9,10,14]. Cachexia has negative implications for patients with breast and gynecologic cancer; therefore, the increase in survivorship has been an increase in focus on understanding mitochondrial dysfunction, with the aim to understand how to improve quality of life for [10].

Previous studies have relied on more invasive tools to assess pathological progression of mitochondrial [15,16]. Muscle biopsies have been the gold standard assessment but can cause significant discomfort to the patient [17]. Additionally, muscle biopsies may not represent *in vivo* activation of the skeletal working muscle tissue associated with [17]. Magnetic Resonance Spectroscopy (MRS) provides *in vivo* measurements but is cost prohibitive, time intensive, requires technical expertise, and competes with other clinical needs within the [17]. Metabolic ventilatory measures have been established as a gold standard in evaluation of pathophysiology with many chronic diseases except for large scale studies in cancer chemotherapy treatment [18–20]. These measurements could provide critical mechanistic understanding of oxygen delivery and utilization from a systematic whole-body approach [21]. To understand local skeletal muscle oxygen uptake kinetics, Near Infrared Spectroscopy (NIRS) has been validated with muscle biopsies and [22,23], as a low cost, non-invasive alternative assessing mitochondrial capacity in clinical [17]. NIRS measurement of tissue oxygenation has been well studied and a thorough background on NIRS can be found elsewhere [17,22,24,25]. Briefly, biological tissue has a relatively good transparency for light in the near infrared region (700–1300 nm) and transmits photons through organs for *in situ* monitoring. The refracted light is converted into grams of oxyhemoglobin (O_2_Hb) and deoxyhemoglobin (HHb) based on the modified Beer-Lambert law [26]. NIRS devices with multiple transmitters at different distances from the receiver can calculate the Tissue Saturation Index (TSI)=O_2_Hb/(O_2_Hb + HHb) and reflects the percentage of measured blood that is oxygenated.

Assessment of mitochondrial capacity with NIRS includes studies of clinical populations with peripheral artery [27], chronic kidney [24], and neurologic diseases such as traumatic spinal cord injury and multiple [22], as well as comparisons with healthy [28] and age-related differences in skeletal muscle oxidative [17]. However, there is a dearth of NIRS studies examining the effects of chemotherapy on skeletal muscle mitochondrial function in patients with cancer. Only two studies to our knowledge have utilized NIRS to measure muscle oxygenation variables in cancer survivors. Ederer, et al. [29] determined that [HHb] and [Hb]total were significantly lower in eight cancer survivors (all eight received chemotherapy and five received radiation) compared to healthy controls during exercise at ventilatory threshold. Grigoriadis et al. [30], did not find a significant difference in muscle oxygenation variables between 23 patients with breast cancer (16 received chemotherapy, nineteen received radiation therapy, and 21 received hormonal therapy) and 23 participants who served as age and BMI matched controls. Recent literature of near infrared spectroscopy related to cancer primarily involves detection and identification of cancerous [31] or the use of near infrared light as a photoimmunotherapy [32]. Therefore, the hypothesized loss of mitochondrial capacity throughout chemotherapy treatment has not been studied longitudinally starting at baseline and tracking through the chemotherapy regimen in breast and gynecologic cancer patients with NIRS to date.

The aims of our study are to develop a protocol that 1) assesses mitochondrial dysfunction in cancer patients using exercise that is tolerable for the patients throughout the entire chemotherapy regimen and 2) observe the changes in mitochondrial functional capacity between different chemotherapy regimens for each chemotherapy cycle. The protocol also will help us evaluate a potential correlation between subjective self-reported fatigue and perceived effort with corresponding objective whole-body metabolic measurements and NIRS measurements. The proposed study will help inform clinical decision makers in the oncology community regarding current chemotherapy regimens (based upon the National Comprehensive Cancer Network, NCCN) that patients may best tolerate for cachexia and fatigue.

## Materials and methods

### Organization and conduct

The study protocol (Fig 1) was approved in July of 2021 by the Prisma Health Office of Human Subjects Protection Institutional Review Board Committee C (Protocol # Pro00110826). This study is sponsored through the Prisma Health Cancer Institute Office of Philanthropy and Partnership, the University of South Carolina School of Medicine Greenville Summer Scholars Program, and Furman University. The study sponsors and funders, played no role in study design; collection, management, analysis, and interpretation of data; writing of the report; and the decision to submit the report for publication, including whether they will have ultimate authority over any of these activities. This clinical trial has been registered with clinicaltrials.gov (Identifier: NCT006672497). Data collection started on July 26, 2021 and is ongoing through March 27, 2026. The authors confirm that all ongoing and related trials for this observation trial (no drug or intervention) are registered.

**Fig 1 pone.0315351.g001:**
[figure not shown]
Schedule of enrollments, interventions, and assessments.

### Experimental design

We will use an observational mixed model repeated measures design to longitudinally compare (pre-chemotherapy and throughout treatment) patients’ skeletal muscle mitochondrial capacity of the vastus lateralis during stationary cycling. ANOVAs will be used to assess this same mitochondrial capacity between chemotherapy regimens at each chemotherapy cycle. Pearson or spearman correlations will be used to assess relationships between self-reported fatigue and effort values and metabolic measurements (whole-body as well as NIRS). The study population will include female patients with breast or gynecological cancer. All testing will take place in the University of South Carolina School of Medicine Greenville’s Human Performance Laboratory in the Prisma Health Cancer Institute.

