### Observational protocol for first and subsequent visits

Before starting chemotherapy, patients will undergo baseline testing that includes a lactate threshold test and an ON-OFF kinetics exercise test. The lactate threshold test will determine the power output (110% power at lactate threshold, P_LT+_) to be used for the follow-up baseline on-off kinetics test (ON-OFF). The ON-OFF kinetics test will take place at least 24 hours after the lactate threshold test and consist of 3 cycles of 2 minutes at P_LT+_ and 2 minutes of complete rest. Whole body O_2_ uptake and CO_2_ production will be captured via a metabolic cart during each test. Testing will take no more than 60 minutes per session, with a maximum study total of 300 minutes (about 5 hours) of participation per patient. Patients will be requested to avoid exercise and use of certain substances (tobacco, alcohol, caffeine, and contraindicated medications) 24 hours before testing. If laboratory baseline evaluation cannot be completed prior to the participant’s treatment initiation, treatment will not be delayed, and patients will be waived from the study.

The independent variables in this study are drug regimen and number of chemotherapy treatments. The dependent variables in this study will be the changes in O_2_Hb, HHb, and TSI of the vastus lateralis, indicative of mitochondrial oxidative capacity after a bout of cycling. The specific variables measured will be the average recovery kinetics time constant, τ, and TSI. Indirect calorimetry (O2 uptake, CO2 production) also will be captured at rest and during the ON/OFF kinetics as control variable comparisons for whole-body O2 uptake and utilization.

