#### Fatigue and quality of life surveys.

We will administer the Mini-Mental State Exam (MMSE) [43–45], Brief Fatigue Inventory (BFI) [46], Physical Activity Intake [47,48], PROMIS Global Health [49,50], and GLTPAQ surveys [51] prior to participant engagement in cycling exercises at the beginning of the first visit. We will administer BFI, PROMIS Global Health, and Physical Activity follow-up surveys at the beginning of each individual study session to assess any changes in cancer related fatigue associated with chemotherapy treatment that may develop throughout the study period.

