### Outcome measures

#### Collection of biometrics at each visit.

Study staff will measure O2Hb, HHb, and TSI, via the NIRS PortaMon device during the on-off kinetics protocol. We also will measure ventilatory whole-body components including O_2_ and CO_2_ via the Parvomedics metabolic cart. Participants’ perceived exertion to the exercise will be measured via RPE during every exercise stage.

NIRS data will be collected using Artinis Medical System’s Oxysoft software at a frequency of 10hz. A differential pathlength factor (DPF) value of 4 will be selected, as recommended by Artinis (Einsteinweg, Netherlands). The PortaMon will be placed on the vastus lateralis of participants for a period of at least 10 minutes prior to beginning exercise in accordance with the recommendation of Cortese L, et al. to allow calibration of the PortaMon [53].

Throughout data collection, researchers will closely observe for excess movement from participants that may affect the data collection. These sections will be removed from analysis. After data collection, a moving average with a filter width of 1.5 seconds will be applied to smooth leg movement artifacts that occurred during cycling. Data cleaning and analysis will be conducted using R (R Core Team, 2020] and RStudio (Rstudio Team, 2020].

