We will analyze the *ΔO*_*2*_*Hb,* Δ*HHb,* and *ΔTSI*, calculated as the change in steady state levels of O_2_Hb, HHb, and TSI respectively from work to rest, with steady state values calculated as the mean value of the final thirty seconds of the stage. For each data set of one on-off kinetics, there will be three work/rest period pairs therefore we will calculate three delta values and average the three delta values to obtain one delta value for O_2_Hb, HHb, and TSI per data set. The three work/rest transitions will allow for reliability testing with intraclass correlation coefficients. For participant data to be included in the final analysis, the participant will need to complete at least three on-off kinetic laboratory visits. Each participant will complete an on-off kinetics at least two weeks apart, but not more than one month apart in accordance with their prescribed chemotherapy treatment regimen. Each on-off kinetics will correspond with the first infusion of a chemotherapy cycle. To allow participants a maximum amount of time to recover from infusions before participating in exercise, the corresponding on-off kinetics takes place within 48 hours of the first infusion of the subsequent chemotherapy cycle. Since chemotherapy treatments vary depending on oncologist recommendation, each participant may complete different lengths of treatment, resulting in each participant having different numbers of data points. This will prevent us from using traditional statistical analysis such as repeated measures ANOVA. Since it is not time itself, but rather the compilation of chemotherapy infusions over time that we predict will cause changes in measures of mitochondrial oxidative function, we will treat the number of chemotherapy cycles as an ordinal variable in this analysis. We will complete an analysis using mixed effects models to predict τ and deltas from the number of chemotherapy treatments with a random intercept for patients. For aim 2, ANOVAs will be used to assess differences in mitochondrial capacity between drug regimens at each chemotherapy cycle.

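### Plain Pearson or Spearman correlations are planned for fatigue and effort measures that repeat within patients: anti-conservative if visits are pooled, silent on within-patient association if not

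*Protocol article*

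**What the plan says.** The correlation analysis serves a goal stated after the two numbered aims in the Introduction: to "evaluate a potential correlation between subjective self-reported fatigue and perceived effort with corresponding objective whole-body metabolic measurements and NIRS measurements". The method is named once, under Experimental design: "Pearson or spearman correlations will be used to assess relationships between self-reported fatigue and effort values and metabolic measurements". It is not mentioned again under Data analysis and statistical analysis.

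Both sides of each correlation are measured repeatedly:

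- Fatigue: the surveys section plans "BFI, PROMIS Global Health, and Physical Activity follow-up surveys at the beginning of each individual study session".
- Effort: "perceived exertion to the exercise will be measured via RPE during every exercise stage", so up to three ratings per on-off visit.
- NIRS and gas exchange are captured during each on-off test. The three τ values within a visit are averaged to one.
- Visits: to enter the final analysis, "the participant will need to complete at least three on-off kinetic laboratory visits", and "each participant may complete different lengths of treatment, resulting in each participant having different numbers of data points".

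The data analysis section does plan a random intercept for patients, but only in the models that predict τ and the deltas from the number of treatments. The regimen ANOVAs are specified separately for each cycle. The correlation sentence carries neither a patient term nor a per-cycle limit.

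**The concern.** Pearson and Spearman tests assume that the pairs are independent. Several visits from one patient are not independent when both variables differ persistently between patients. Entering every visit as a separate pair overstates the information, so p-values become too small and intervals too narrow. The coefficient would also blend two different associations: whether patients with slower recovery tend to be more fatigued (between patients), and whether a patient's fatigue changes as her own recovery changes (within patient). Fatigue could then be reported as linked to muscle oxygenation on inflated evidence, and readers could not tell which association was meant.

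Taking one pair per patient, at a single visit or as patient means, removes the independence problem. It then leaves most of the longitudinal data unused for this question and gives no within-patient answer.

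**Working it through.** **Plan's own figure.** The only stated sample-size result is n = 30 with power 0.8, for the effect of chemotherapy on τ. It cannot be reproduced, because the mean change per cycle, the random-slope SD, alpha and the number of simulated cycles are not given. No power, alpha or expected coefficient is stated for the correlations. The check below therefore concerns their error rate only.

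**Inputs from the Sample size section.** The random intercept of τ is gamma with shape 1.57 and scale 12.5, shifted by 13.25; the error SD is 5.54 s; there are 30 patients.

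- Between-patient SD = 12.5 × √1.57 = 15.66 s.
- ICC of τ = 15.66² / (15.66² + 5.54²) = 245.3 / (245.3 + 30.7) = 0.889.

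**Number of visits, m.** Three is the stated minimum. The visit section says "Testing will take no more than 60 minutes per session, with a maximum study total of 300 minutes". At full length that is 300 / 60 = 5 sessions, or about four on-off visits after the lactate threshold test. The Sample size section mentions 3–4 cycles plus a further 3–4, so more are possible.

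**Assumption.** The ICC of fatigue or effort is not in the document. It was varied from 0 to 0.8.

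**Formula, no true association, visits pooled.** Variance inflation = 1 + (m − 1) × ICC(τ) × ICC(fatigue). Effective pairs = 30m / inflation. Approximate rejection rate = 2 × [1 − Φ(1.96 / √inflation)].

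Worked case, m = 4 and fatigue ICC 0.5: inflation = 1 + 3 × 0.889 × 0.5 = 2.33. The 120 pairs carry the information of 120 / 2.33 ≈ 51. A correct interval is about √2.33 = 1.53 times as wide. The approximate rejection rate is 19.9%.

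**Simulation check.** 6,000 data sets per setting, 30 patients with m visits each, τ from the plan's gamma and error SD, fatigue independent of τ, and no trend over cycles.

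| Visits | Fatigue ICC (assumed) | Inflation | Effective pairs | Approx. rate | Pooled Pearson | Pooled Spearman |
|---|---|---|---|---|---|---|
| 3 | 0 | 1.00 | 90 of 90 | 5.0% | 5.2% | 5.2% |
| 3 | 0.3 | 1.53 | 59 of 90 | 11.3% | 10.5% | 10.6% |
| 3 | 0.5 | 1.89 | 48 of 90 | 15.4% | 16.3% | 15.2% |
| 3 | 0.8 | 2.42 | 37 of 90 | 20.8% | 21.1% | 19.3% |
| 4 | 0 | 1.00 | 120 of 120 | 5.0% | 5.1% | 5.2% |
| 4 | 0.3 | 1.80 | 67 of 120 | 14.4% | 14.2% | 13.2% |
| 4 | 0.5 | 2.33 | 51 of 120 | 19.9% | 20.6% | 18.8% |
| 4 | 0.8 | 3.13 | 38 of 120 | 26.8% | 27.5% | 25.2% |

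With six visits and a fatigue ICC of 0.3 to 0.8, pooled Pearson rejects in 19.4% to 37.2%.

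In the same data sets, a single visit, patient means and a within-patient (repeated-measures) correlation all reject in 4.4% to 5.7%.

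**Sensitivity to the τ ICC.** The gamma parameters imply a mean τ of 1.57 × 12.5 + 13.25 = 32.9 s, whereas the section states an average of 25.35 s. Keeping the shape and shift and matching 25.35 s gives an SD of (25.35 − 13.25) / √1.57 = 9.66 s, and an ICC of 9.66² / (9.66² + 5.54²) = 0.752. At m = 4 and fatigue ICC 0.5, inflation is then 1 + 3 × 0.752 × 0.5 = 2.13 and the approximate rate is 18%. The conclusion does not depend on which figure is used.

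**The case against.** The strongest reply is that the protocol never says visits are pooled. A reader might infer from the bare method name that the p-values and intervals will be far too optimistic; the text does not support that as a statement of fact. The ANOVAs in the preceding sentence are run at each cycle, so a per-cycle correlation with one pair per patient is a possible reading, and it holds about 5% per test. The authors clearly know that the data are repeated, since they choose mixed models for τ and the deltas. This is also a condensed article, and the unit of analysis may be set out in a fuller document. All of this stands, and it makes the error-rate part conditional.

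It is also true that the fatigue ICC is assumed, that no ICC is available for RPE, the deltas or gas exchange, and that the analysis is exploratory, unpowered and part of a pilot. Nor does the document explicitly ask whether fatigue tracks τ within a patient: it asks for a correlation with corresponding measurements, and links changes in fatigue to chemotherapy.

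What the reply does not remove is that a method has been named, and that the named method fits the data poorly under either reading. Pooled, it is anti-conservative wherever fatigue differs persistently between patients. With one pair per patient it is valid, but it does not use the repeated pairs to examine change within patients.

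**Conclusion.** The point holds in conditional form. The plan commits to plain correlation for measures taken at least three times per patient and provides no patient term or visit restriction for it.

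- **If visits are pooled:** a nominal 5% Pearson test rejects in about 10–21% of null data sets at three visits and 14–28% at four. This rests on the plan's τ ICC of 0.889, an assumed fatigue ICC of 0.3–0.8, equal visit numbers and no trend over cycles. With a fatigue ICC of 0 there is no inflation. The coefficient mixes between- and within-patient association.
- **If done per visit or on patient means:** error is about 5% per test, but within-patient association is not addressed.

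The two numbered aims and the stated sample size are not affected. It should be settled before analysis: the Trial status section reports 26 participants complete of a planned 30.

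**What to change.** State the unit of analysis and replace the plain correlation for repeated data with one of:

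- a repeated-measures (within-patient) correlation; or
- a mixed model for the fatigue or effort score with a random patient intercept, in which the NIRS or metabolic measure is split into the patient's mean and the visit's deviation from that mean.

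Report the within- and between-patient associations separately. Keep Pearson or Spearman only where there is one pair per patient: any single visit, or patient means. State also how the RPE ratings within a visit are combined, for example by averaging them as is done for τ. Label the analysis as exploratory.

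The cost is analysis code only, with no added visits or data. Relative to pooling, intervals widen, by a factor of about 1.5 in the worked case with four visits and a fatigue ICC of 0.5.
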